#### Mediation and moderation analyses

2.8.2

Mediator and moderator analyses are exploratory and follow the principles by Kraemer et al. (Kraemer et al., 2002). Chronotype will be examined as moderator of the intervention effect on insomnia, by adding the variable to the linear mixed models of insomnia severity as an interaction term (e.g. time x group allocation x moderator). If chronotype will have a significant interactive effect with treatment on the outcome, it is a moderator; with main effect and no interactive effect it is a predictor of response (Kraemer et al., 2002). Additionally, an exploratory investigation of the potential moderating variables will be conducted, including sociodemographic variables and symptom severity, without pre-defined hypotheses, by using the QUINT method (Qualitative Interaction Trees) (Dusseldorp et al., 2016a). The QUINT method identifies three participant subgroups based on baseline characteristics: one where the intervention is more effective, one where the control is more effective, and an optional third where both are equally effective. It includes multiple moderators simultaneously without predefined interactions, detecting higher-order interactions, and represents results as an easy-to-interpret binary tree (Dusseldorp et al., 2016b). Outcome expectations, adherence, and stressful life events will be tested as predictors of treatment response. Furthermore, predictors of adherence, such as demographic variables, symptom severity, and stressful life events, will be investigated.

Light exposure, circadian shift, variability in sleep patterns, pre-sleep arousal, and dysfunctional beliefs and attitudes about sleep will be evaluated as potential mediators of the intervention effect on insomnia severity. The mediators are measured at three time points (T0, T1, and T2), allowing to examine whether treatment-induced changes in mediating variables at T1 predict subsequent changes in outcome at T2. Mediation analysis will be conducted by using multilevel structural equation modeling in R (Preacher et al., 2010), with insomnia severity as dependent variable (Y), group allocation as independent variable (X), and the potential mediator variables (M). All mediators will be investigated separately first and significant mediators will be included in a combined model.

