### Aims and hypotheses

1.1

The objective of this study is to evaluate the effectiveness of the guided online ‘*i*-*Sleep & BioClock*’ intervention in reducing insomnia in university students compared to an online psychoeducation control program. We hypothesize that the intervention group will show significantly more improvement in insomnia severity (primary outcome) than the control group at post-test, which will be maintained at 18-week follow-up. Similarly, we expect significant improvements in secondary outcomes assessed by the sleep & light exposure diary, depression and anxiety symptoms, functioning, academic performance, and quality of life. Since young adults are more prone to eveningness (Roenneberg et al., 2007), we expect that chronotype will on average shift toward morningness. Additionally, social jetlag is expected to decrease in both groups since fixed bedtimes are recommended.

The secondary aim of this study is to explore potential mediators of the intervention effect. Cognitive mediators, such as pre-sleep arousal and dysfunctional beliefs and attitudes about sleep were found to be mediators of the effect of CBT-I interventions in the adult population, which is why we hypothesize that they will be mediators in the student population too (Lancee et al., 2019; Parsons et al., 2021). Moreover, light exposure, circadian shift, and variability in sleep patterns will be examined as behavioural mediators (Schwartz and Carney, 2012).

The third aim of the study is to investigate potential moderators of treatment response, in order to determine who benefits most of the intervention. We hypothesize that chronotype influences the responsiveness to CBT-I, but not to online psychoeducation since the *‘**i-Sleep & BioClock**’* intervention includes intervention elements specifically targeting the biological clock. Other variables, such as sociodemographic variables and symptom severity, will also be tested as moderators, using tree-based interaction models. Outcome expectations, adherence to the program, and stressful life events are expected to be predictors of treatment response (Constantino et al., 2018; Li et al., 2019).

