### Outcome measures

2.6

The outcomes will be evaluated at baseline (T0), 6 weeks (T2), and 18 weeks (T3) after randomization. The T2 measurement is the primary endpoint. Additionally, insomnia severity and the two cognitive mediator variables (DBAS-10 and PSAS) will have an extra assessment point at 3 weeks (T1) after randomization. The questionnaires will be sent out via email and will be filled out in a secured online environment. Participants will be compensated for completing the T2 questionnaires (€15,- voucher) and T3 questionnaires (raffle of eight vouchers of €50,-). Table 2 shows an overview of the assessment instruments used for each time point.

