##### Munich Chronotype Questionnaire (MCTQ)

2.6.2.1

We will assess the 17-item MCTQ, which is a relatively objective self-report questionnaire, since it deals with specific sleep- and wake times. The MCTQ asks for sleep- and wake-times on work/study days and on free days over the past four weeks. Based on this, we can calculate *social jetlag* (the difference in mid-sleep between work/study days and free days), *average weekly sleep duration*, and *average weekly light exposure*, which will be reported as secondary outcomes. We can also determine the *chronotype* (the midpoint between sleep on- and offset on free days corrected for sleep debt accumulated over the workweek), which will be assessed as a moderator (Roenneberg et al., 2003). The MCTQ mid-sleep point shows high correlation with dim light melatonin onset, which is the gold standard for assessing central circadian timing in humans (Kantermann et al., 2015).

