##### Sleep & light exposure diary

2.6.2.7

The sleep and light exposure diary will be assessed in the first seven days after baseline measurement (week 1) and in the seven days after the post-test measurement (week 7). The sleep diary is based on the Carney consensus sleep diary and the light exposure items on the Harvard Light Exposure Assessment (Carney et al., 2012; Bajaj et al., 2011). Text adaptations were made in consensus with a group of sleep researchers. Outcomes that will be derived from this diary will be *sleep onset latency* [SOL; number of minutes from lights off to sleep onset], *wake after sleep onset* [WASO; number of minutes awake between sleep onset and final awakening], *early morning awakening* [EMA; number of minutes between final awakening and getting up], *number of awakenings* [NA], *time in bed* [TIB; number of minutes between lights off and getting up], *total sleep time* [TST; TST = TIB – SOL – WASO - EMA], *sleep efficiency* [SE; SE = TST / TIB x 100]. Students also rate their *sleep quality* and how *rested* they feel in the morning [both rated from 0 to 10]. Additionally, *timing and duration of light exposure* and *screen use before bedtime* [Yes/No] will be assessed. Diary items are described in detail in a supplementary file.

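### The mediation plan claims T0, T1 and T2 measurements for all five mediators, but three of them have no scheduled T1 assessment to support the T1-to-T2 ordering

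*Protocol article*

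**What the plan says.** Section 2.8.2 (Mediation and moderation analyses) sets out the candidates: "Light exposure, circadian shift, variability in sleep patterns, pre-sleep arousal, and dysfunctional beliefs and attitudes about sleep will be evaluated as potential mediators". The next sentence gives their schedule, "The mediators are measured at three time points (T0, T1, and T2"), and its purpose: "allowing to examine whether treatment-induced changes in mediating variables at T1 predict subsequent changes in outcome at T2". No mediator is excepted, and the paragraph closes by saying that all of them will be examined, first singly and then, if significant, in a combined model.

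Section 2.6 (Outcome measures) is narrower: "insomnia severity and the two cognitive mediator variables (DBAS-10 and PSAS) will have an extra assessment point at 3 weeks (T1) after randomization". Section 1.1 (Aims and hypotheses) puts the remaining three in a separate class: "light exposure, circadian shift, and variability in sleep patterns will be examined as behavioural mediators".

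Two instruments in the article could supply those three. The MCTQ is listed in section 2.6.2 among the secondary outcomes, which are given at T0, T2 and T3. On its recall period the article says: "The MCTQ asks for sleep- and wake-times on work/study days and on free days over the past four weeks". The sleep and light exposure diary is assessed in the week after baseline and again "in the seven days after the post-test measurement (week 7").

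**The concern.** A mediation claim needs the mediator to change before the outcome does. The T1 assessment is the design feature meant to provide that order, and section 2.8.2 relies on it for the whole list. If light exposure, circadian shift and sleep regularity are first measured after baseline at T2 or later, an association with T2 insomnia severity has two readings: the programme changed light exposure and timing, which improved sleep; or sleep improved, and light exposure and timing followed. The data could not separate the two.

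The affected mediators are those tied to the biological-clock components, which the Background presents as the addition to existing CBT-I. Exploring mediators is also the trial's stated secondary aim. If the sentence stands, the results paper may claim a temporal order for these mediators that the schedule does not support.

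**Working it through.** No figure in the plan needs reproducing. The check sets each mediator against the schedules given in sections 2.6, 2.6.2, 2.6.2.1 and 2.6.2.7.

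| Mediator (2.8.2) | Possible source | Scheduled assessments | T1? |
|---|---|---|---|
| Pre-sleep arousal | PSAS | T0, T1, T2 | Yes |
| Dysfunctional beliefs | DBAS-10 | T0, T1, T2 | Yes |
| Light exposure | MCTQ or diary | T0, T2, T3 or weeks 1, 7 | No |
| Circadian shift | MCTQ or diary | T0, T2, T3 or weeks 1, 7 | No |
| Sleep-pattern variability | MCTQ or diary | T0, T2, T3 or weeks 1, 7 | No |

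The schedule for the first two rows combines section 2.8.2 with the extra T1 point in section 2.6. The article does not name the source for the last three rows, so both candidates are shown; the last column is the same for either. Adverse events and stressful life events are also asked about at T1, but they are not mediators.

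**Count.** Mediators with a scheduled T1 value: 2 of 5. Without: 5 − 2 = 3, and 3/5 = 60%. This is a share of the listed variables, not a measure of bias.

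**If the MCTQ is the source.** The first post-baseline value is at T2, the same assessment as the outcome. With four weeks of recall at week 6, the window opens at 6 − 4 = week 2 and closes at week 6. It spans T1 (week 3) and runs up to the outcome assessment, so it cannot be split into change before T1 and change after.

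**If the diary is the source.** The follow-up falls in week 7, after the T2 insomnia score at week 6, so the mediator is recorded after the outcome it would have to predict. The first diary week has a further weakness. It follows the baseline measurement, and section 2.3 has randomization occur automatically once the baseline questionnaires are complete. The week-1 diary is therefore not a clean pre-treatment value.

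**Could week-3 diary entries fill the gap?** Section 2.4 asks intervention students to keep the diary daily, and section 2.4.1 has coaches give feedback on it. Section 2.5 only advises control students to monitor their sleep in it, without a coach. Some week-3 entries may exist, but they are not a defined assessment, and their completeness may differ by arm because diary keeping is supported differently.

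Table 2 is not legible in the text at hand. The sections above are explicit enough to settle the point without it.

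**The case against.** The strongest reply is that the harm is small. Section 2.8.2 opens by calling the mediator and moderator analyses exploratory, and the effectiveness analyses do not depend on this sentence. That stands, and it limits the weight of the point. It does not make the sentence accurate.

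Three stronger readings are tempting, and the document does not support them.

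- A reader might infer that the T1-to-T2 test cannot be run at all for the behavioural mediators. Unscheduled week-3 diary entries may exist, so the supportable statement is that no scheduled T1 assessment exists.
- A reader might infer that mediator and outcome are in reversed order for all three. That follows only if the week-7 diary is the source. The MCTQ yields light exposure, social jetlag and chronotype and is given at T2; from it the problem is concurrence, not reversal.
- A reader might infer that the plan declares temporal order to be established. It says only that the schedule allows the question to be examined, which is correct for PSAS and DBAS-10.

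It could also be said that the sentence was meant for the two cognitive mediators only. The sentence before it lists all five and the paragraph ends by referring to all of them, so the text does not read that way. If that was the intention, the wording still needs correcting and the other three have no stated temporal design.

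**Conclusion.** The point holds as an internal contradiction. Section 2.8.2 attributes a T0, T1 and T2 schedule to five mediators, and the rest of the protocol provides it for two. For light exposure, circadian shift and sleep-pattern variability, no scheduled measurement supports the T1-to-T2 ordering.

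This assumes that the MCTQ and the diary are the only possible sources, since no other instrument described in the article measures these quantities. It does not depend on which of the two is used. The consequence is confined to the interpretation of exploratory mediation results; the primary comparison is unaffected. The correction should be made before analysis so that source and lag are not chosen after seeing the data.

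**What to change.** In section 2.8.2:

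1. Limit the three-time-point sentence and the T1-to-T2 test to PSAS and DBAS-10.
2. Name the source instrument for light exposure, circadian shift and sleep-pattern variability. Analyse and report these three as concurrent association, without a claim of temporal order, and carry that label into the combined model if any of them enters it.
3. Optionally add a supplementary analysis of the T2 (MCTQ) or week-7 (diary) mediator against T3 insomnia severity, adjusted for T2 severity. State that it addresses later change or maintenance, not the T0-T2 effect. It should not be the default: section 1.1 expects the effect to be present at post-test and then maintained, so a null result here would say little about what produced it.
4. Use week-3 diary entries only as a sensitivity analysis. Report completeness by arm, and note the differing support for diary keeping and the post-baseline timing of the week-1 diary.

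The cost is wording and a few lines of analysis specification. Items 1 to 3 need no new data collection, since T3 insomnia severity is already scheduled; item 4 is possible only if entries exist. The price is a weaker claim for the behavioural mediators and, for the supplement, fewer observations at T3 because of drop-out, which section 2.7 expects to be high (50%).

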## Discussion

3

Sleep and mental health problems are highly prevalent among university students (Auerbach et al., 2018). They are impairing students' functioning, wellbeing, and quality of life, and can have far reaching long-term consequences (Baglioni et al., 2011). There is a great need for easily accessible and effective interventions to treat insomnia and the related psychological problems among students. In the adult population, internet-based CBT-I has already been proven to be beneficial for improving sleep other mental health complaints (Espie et al., 2019; Zachariae et al., 2016; van der Zweerde et al., 2019b). In the population of university students the research is still more scarce.

This study protocol presents the design of a randomized-controlled trail, to investigate the effectiveness of a guided e-health intervention *‘i-Sleep & BioClock’* in university students. The primary aim of this study is to investigate whether such an intervention can help students to overcome their insomnia complaints. The secondary aim is to investigate whether mental health symptoms improve due to the intervention and whether the effects are maintained in the longer term. Thirdly, moderators, mediators, and predictors of response will be evaluated in order to understand how and for whom the intervention works.

The current study shows several strengths. Firstly, this is a pragmatic randomized controlled trial because it is conducted in a real-life setting, improving its external validity and making the results generalizable. Secondly, a previous pilot study has been conducted to minimize errors in the trial. Thirdly, the analysis will follow the intention-to-treat approach, which is a method known to reduce bias and provide a realistic estimation of the effectiveness. Lastly, *‘**i-Sleep & BioClock**’* is a low-threshold intervention, as it is easily accessible from any location and device with internet connection, at any time without the constraints of a formal intake or appointment, office hours or therapist schedules, and the possibility to register anonymously and receive help without having to fear stigma. It requires less resources than traditional CBT-I and in case it is effective it could be implemented immediately on a larger scale. Additionally, several potential limitations of the study should be noted. Firstly, our last follow-up moment is at 4.5 months after baseline, making it impossible to draw conclusions about the long-term effects of the intervention. Secondly, despite the fact that we examine many different outcome measure, all of those are self-report measures. Thirdly, all contact with participants is online or via the phone, which might lead to higher drop-out than in face-to-face interventions. Nevertheless, this approach is most fitting to the low-threshold characteristic of the intervention and moreover it minimizes burden for participants. High drop-out rates are common in e-health interventions and we indeed expect a high drop-out rate, where data might not be missing at random. However, we will implement different strategies to enhance completion of the intervention and measurements, such as phone calls by the e-coach, reminders, and monetary incentives to complete the questionnaires. Lastly, the exclusion of students with suicidal ideation limits the generalizability of the findings.

Preventing exacerbation of mental health problems among students is a very important step toward reducing the burden of mental health problems among this vulnerable group. Early interventions should be prioritized to avoid the manifestation of more severe mental health conditions. In case the online self-help intervention is effective in university students, this might encourage the dissemination of the *‘**i-Sleep & BioClock**’* intervention in universities worldwide.

## Abbreviations

Cognitive Behavioural Therapy for InsomniaCBT-IEarly morning awakeningEMAGeneralized Anxiety Disorder ScaleGAD-7Dysfunctional beliefs and attitudes about sleepDBAS-10Duration of Sleep EpisodeDSEInsomnia Severity IndexISIMunich Chronotype QuestionnaireMCTQMental Health Quality of Life QuestionnaireMHQoLNumber of awakeningsNAPatient Health QuestionnairePHQ-9PsychoeducationPERandomized controlled trialRCTPre-Sleep Arousal ScalePSASSleep efficiencySESleep onset latencySOLTime in bedTIBTotal sleep timeTSTWake after sleep onsetWASOWork and Social Adjustment ScaleWSAS

## Trial status

Start of recruitment: November 2023.

End of recruitment: planned for July 2024.

## Ethics approval and consent to participate

The study protocol was approved by the METC Leiden Den Haag Delft on July 17th 2023 (NL83395.058.23). Written digital informed consent to participate will be obtained from all participants.

## Consent for publication

Not applicable.

## Data Availability

The datasets generated and analysed during the current study are available from the corresponding author on reasonable request, and in the DANS repository after study completion.
